## Background

### Falls and hip fracture in older people

Approximately 30% of home-dwelling people aged 65+ fall each year, and half of them fall twice or more. Ten percent of the falls result in serious injuries [1]. Multimorbidity and frailty often complicate the assessment of falls amongst older people. Scandinavian countries have the highest reported incidence of hip fractures (cervical or trochanteric) in the world [2], 90% of which are related to a fall. Hip fractures are associated with considerable mortality [3,4]. Due to the increasing number of older people, the demand for treatment, rehabilitation and care for hip fracture patients will increase steeply during the coming years. Older people with hip fracture after a fall have more comorbidity, dementia and physical disability than older people who fall without developing a fracture [5].

In a retrospective study carried out among patients surviving a hip fracture at Ullevaal University Hospital, the one-year mortality was 23%, and the number of institutionalised patients rose from 15% before the fracture to 30% after one year. The number of patients dependent on a walking aid increased from 35% before the fracture to 76% after one year, 43% of the patients had lost the ability to walk independently outdoors, and 25% had lost the ability to prepare food independently [6].

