### Data analyses and statistical power

The primary analyses will be done in a modified intention-to-treat analysis including the sample of patients completing the CERAD 10 words test and CDR at 4 months. The weighting of the components of the primary endpoint (see primary endpoint section above) will be definitely decided upon before any analyses of the treatment effect are initiated. A separate per protocol analysis will be undertaken. The primary endpoint will be analysed by stratified linear regression. If the assumption of normality turns out to be violated, additional analyses will be performed on transformed data as well as by non-parametric methods (Mann–Whitney test). Binary outcomes will be analysed by chi square tests and logistic regression models. The material will be checked for any inequality in the distribution of important prognostic variables between the two arms, and if such are present, they will be adjusted for by including these in appropriate regression models.

Sensitivity analyses will be performed by imputing missing values in different conservative ways, e.g. by imputing the worst observed score of the treatment group and also by random sampling from the observed scores in the treatment group.

The main analyses of 12 months data will be carried out including patients with responses registered at that time point. Additional sensitivity analyses will be performed in the sample of all randomised patients using different methods of imputation as described above as well as by carrying the four month observation forward.

If an interaction test is statistically significant at the 0.10 level, we will analyse the effect upon the endpoints separately in the following subgroups: patients admitted from nursing homes or not, and patients with and without pre-fracture dementia.

We also register the time window from admittance to start of surgery, as any group difference here may also impact severely on the outcome [7].

No data are available allowing us to carry out precise power estimates based on our primary endpoint. Based upon previous experiences with CDR, however [61] ([name], unpublished data), we judge 300 patients to be sufficient to detect clinically meaningful differences. As 20% of hip fracture patients can be expected to die before the 4 months follow up [6], we aim for 370 patients to be randomised.

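### Imputation from the patient's own arm is labelled conservative but is not, may overstate precision, and can give cognition scores to patients who died

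*Protocol article*

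**What the plan says.** All of this is in the protocol article, section Data analyses and statistical power.

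- The primary analysis uses only patients who complete both the word-list test and the CDR at 4 months. Nothing is imputed there.
- Sensitivity analyses fill in missing scores by methods described as conservative. Two examples are given: "by imputing the worst observed score of the treatment group and also by random sampling from the observed scores in the treatment group". It is left open whether a value is drawn once or repeatedly, how repeated draws would be combined, and which arm is meant by the treatment group.
- At 12 months the main analysis again uses responders. The sensitivity analyses extend to everyone randomised, "using different methods of imputation as described above as well as by carrying the four month observation forward".
- The only source of missing outcomes that the section counts is death: "As 20% of hip fracture patients can be expected to die before the 4 months follow up".

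**The concern.** The primary analysis set is selected after randomisation, by survival and by completing the tests. The imputation analyses are the only stated check on that selection, so they need to show what happens if the missing patients differ from the completers. A method that assumes the missing resemble their own arm's completers cannot show this. If its filled-in values are also counted as real observations, it reports more precision than the data contain. A reader told that a conservative analysis agreed with the main one would be reassured without good reason. Giving a patient who has died a cognition score raises a separate problem, because the quantity being estimated then has no clear meaning.

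**Working it through.** **Inputs.** From the article: 300 evaluable patients judged sufficient, 20% dead by 4 months, target 370, 332 randomised in equal groups (166 per arm), and one-year mortality of 23% (Background, Falls and hip fracture in older people). Assumed: two-sided alpha of 0.05, because the article gives none for the treatment comparison.

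**The plan's own figure.** 300/(1 − 0.20) = 375, against "we aim for 370 patients to be randomised". Read the other way, 370 × 0.80 = 296. The target is reproduced to within rounding, so 20% is the share missing that the plan itself works with. For the 332 actually randomised, 332 × 0.80 ≈ 266.

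**Random draws from the own arm: direction.** A drawn value has the arm's completer mean as its expectation. The filled-in arm mean, and so the difference between arms, equals the completers' value in expectation. This holds for one draw or for many.

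**Random draws from the own arm: precision with one draw per missing value.** Let an arm have N patients, a fraction f missing, n = N(1 − f) completers and variance s².

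- True variance of the filled-in mean: s²/n + [(N − n)/N²]s² = (s²/N)[1/(1 − f) + f].
- Variance used by the naive test: s²/N.
- Ratio: R = 1/(1 − f) + f.
- Type I error: 2[1 − Φ(1.96/√R)].

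| Share missing f | R | SE understated by √R | Type I error |
|---|---|---|---|
| 10% | 1.111 + 0.10 = 1.211 | 1.10 | 0.075 |
| 20% | 1.25 + 0.20 = 1.45 | 1.20 | 0.104 |
| 23% | 1.299 + 0.23 = 1.529 | 1.24 | 0.113 |

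Simulation with 332 patients at 20% missing agrees: 0.104 with normal scores and 0.101 with scores bounded at 0 to 100 (20,000 runs each). A stratum-adjusted regression gave 0.098 (5,000 runs; assumed 30% from nursing homes and a stratum effect of 1.5 SD).

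**How far this depends on the reading (20% missing, simulated type I error).**

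| Procedure | Type I error |
|---|---|
| One draw, own arm | 0.101–0.104 |
| Repeated draws, own arm, Rubin's rules (20 imputations) | 0.052 |
| All draws from the intervention arm | 0.049–0.050 |
| Draws from both arms pooled | 0.048–0.052 |
| Own-arm worst score, equal missingness | 0.073 (normal), 0.012 (bounded) |
| Completers only | 0.049 |

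**Own-arm worst score: direction.** Suppose both arms have completer mean μ and worst score w, with fractions f_C (control) and f_I (intervention) missing. Filling with w moves the difference (intervention minus control) by (f_C − f_I)(μ − w). The sign follows whichever arm has more missing. As an illustration with assumed values μ = 55, w = 0 and 5 percentage points more missing in controls, the shift is 0.05 × 55 = 2.75 points towards the intervention. With the imbalance reversed, it is 2.75 points against it.

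**Deaths and carry-forward.** The 12-month imputations cover everyone randomised, which includes the dead, and the general imputation sentence makes no exception for them. Carry-forward needs a 4-month score. With 20% dead by 4 months and 23% by one year, it could reach at most about 3 percentage points of the deaths. For survivors it assumes no change between 4 and 12 months. Yet the Discussion describes nursing home residents and other very frail participants as at high risk of new or worsening dementia.

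**The case against.** The case against is substantial. The methods are introduced as examples in a condensed article, and the number of draws and how they are combined may be set out in a plan not shown here. Neither the single draw nor the own arm is stated; with proper repeated draws, or with all draws from the intervention arm, the error stays near 5%. The conditions attached to the inflation are therefore necessary. The label does not depend on the number of draws: even repeated own-arm draws return the completers' difference. It does depend on the own-arm reading. That is the likelier one, because the article elsewhere calls the orthogeriatric arm the intervention or experimental group.

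Three stronger readings are tempting, and the document does not support them.

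- *The trial's type I error doubles.* It does not. The primary test uses completers without imputation, and the inflation concerns one supportive analysis.
- *None of the planned imputations is conservative.* With equal missingness and bounded scores, the worst-score method gave 0.012, well below 5%. It can be conservative, but nothing in the plan guarantees it.
- *Every method gives scores to all the dead, and most missing values are deaths.* Carry-forward cannot reach patients who died before 4 months. The article gives no rate for missing data other than deaths.

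The article also plans to recover missing proxy information by telephone and reports mortality as its own endpoint. Both help, but neither says how the dead are treated in these analyses.

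**Conclusion.** The point holds in conditional form. On the own-arm reading, the random-draw analysis is wrongly called conservative, because it reproduces the completers' difference in expectation. If each value is also drawn once and treated as observed, a nominal 5% test has about 10% type I error at 20% missing and about 7.5% at 10%, with a two-sided alpha of 0.05 assumed. Own-arm worst-score imputation has no guaranteed direction. Patients who died can be given cognition scores: at 12 months because the sample is everyone randomised, and at 4 months because deaths are not excepted. The primary analysis stands as it is, so this is a should-fix matter about how far the supportive analyses can be trusted.

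**What to change.** 1. Stop describing own-arm random draws as conservative, and state that own-arm worst-score imputation depends on the balance of missingness between arms.
2. Separate patients who died from survivors with missing scores, and report the numbers by arm.
3. For survivors, replace the random draw with multiple imputation combined by Rubin's rules, using data already collected: randomisation stratum, IQCODE, pre-fracture CDR and any observed component of the composite.
4. Add a version that works against the intervention: either shift imputed scores down in the intervention arm only, or draw that arm's missing values from the control arm's distribution.
5. Do not impute cognition for the dead. Report survivors' scores with mortality alongside, or add a supportive worst-rank analysis with death ranked below any score. State that the latter mixes mortality with cognition and will favour the arm with fewer deaths.
6. At 12 months, do not rely on carry-forward as a conservative analysis. A mixed model of the 4- and 12-month scores would not by itself solve the problem, since it implicitly models scores after death unless deaths are handled separately.

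The cost is revised wording, some extra programming and wider intervals in the sensitivity analyses. No new data are needed. The article places the formal effect analyses in summer or autumn 2012 at the earliest, so on its timetable the change could precede them.

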Since the focus of the trial is cognition and prevention of cognitive decline, we have defined wider eligibility criteria than many other hip fracture trials. Nursing home residents and other patients with pronounced frailty are particularly vulnerable to sub-optimal clinical quality, and are at high risk of developing dementia and of worsening of a pre-existing dementia. Accordingly, these patients are included in our study, even though they have a very limited rehabilitation potential with respect to for instance return to own home or independent mobility. Likewise, we have not set a lower age limit for our study, but exclude those who fracture their hip due to a high energy trauma. Nearly every hip fracture patient is above 70 years, but, in our opinion, a hip fracture due to a low energy trauma in a person below 70 is an indicator of frailty, making inclusion in this trial logical. The same reasoning applies to those with pathological fractures, for instance due to malignancy. These patients are also prone to delirium, and thus should be eligible for our study regardless of their potential to achieve independent gait function, unless their life expectancy is very short. Our wide inclusion criteria imply a good external validity, but at the expense of an increased heterogeneity in the patient sample.

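### The main 12-month analysis is completers-only and sets aside observed 4-month scores; the arm contrast is biased materially only if drop-out depends on 4-month cognition differently by arm, and the listed sensitivity analyses do not repair this

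*Protocol article*

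**What the plan says.** All of this is in the Protocol article, Data analyses and statistical power, unless stated otherwise.

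- **Main 12-month analysis.** "The main analyses of 12 months data will be carried out including patients with responses registered at that time point".
- **Back-up analyses by imputation.** "Additional sensitivity analyses will be performed in the sample of all randomised patients using different methods of imputation as described above". The methods referred to are given for the 4-month analysis: "by imputing the worst observed score of the treatment group and also by random sampling from the observed scores in the treatment group".
- **Back-up analysis that reuses the earlier visit.** The same sensitivity analyses are also to be done "as well as by carrying the four month observation forward".
- **Model.** "The primary endpoint will be analysed by stratified linear regression". No repeated-measures model is named. Covariate adjustment is conditional ("The material will be checked for any inequality in the distribution of important prognostic variables between the two arms"), and the 4-month score is not mentioned as a covariate for 12 months.
- **Visits.** The sections Primary endpoint and Data collection have the cognitive composite measured at both 4 and 12 months.
- **Status.** Study objectives puts the primary objective at 4 months; Time plan of the study treats the 12-month results as secondary.
- **Mortality.** The sample-size paragraph expects 20% to die before the 4-month visit. The Background gives 23% one-year mortality in an earlier local study. Both figures cite the same reference.

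**The concern.** A patient assessed at 4 months and lost before 12 months has an observed score on the same scale, and it is informative about the missing one. A completers-only comparison ignores it, so among survivors it relies on missingness being unrelated to cognition within arm, or on the selection being the same in both arms and cancelling in the difference. The intervention is meant to affect cognition, and mortality and residence are also studied as effects, so who remains at 12 months could differ by arm. In that case the 12-month contrast partly reflects who was retained.

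The sensitivity analyses ought to show whether this matters. None of them uses the 4-month score in a way that is valid when patients change between visits, and two of them, applied to everyone randomised, fill in cognitive scores for patients who have died.

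**Working it through.** **1. The plan's own figure.** Target to randomise: 300 / (1 − 0.20) = 375, against 370 stated (within 3%). This confirms that 20% loss by death before 4 months is the working assumption. The base of 300 cannot be reproduced because no effect, SD or power is given. The point here turns on neither number.

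**2. Deaths on the document's rates, 332 randomised.**
- Dead before 4 months: 332 × 0.20 = 66.
- Dead by one year: 332 × 0.23 = 76.
- Dead between visits: 332 × (0.23 − 0.20) = 10.
- Alive at 4 months: 332 × 0.80 = 266; 10 / 266 = 3.75% of them die before 12 months.

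Worst-score and random-draw imputation in all randomised patients would therefore assign scores to about 66 (4-month rate) to 76 (one-year rate) dead patients. Carry-forward can do so only for the roughly 10 who die between visits, because those who die before 4 months have nothing to carry.

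**3. Random draw reproduces the completers' result.** With a proportion m missing in an arm and completers' mean μ, the expected arm mean after drawing from that arm's observed scores is (1 − m)μ + mμ = μ. The arm difference is unchanged on average.

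**4. Size of the bias.** Simulation with about 265 patients alive at 4 months and SD 1 at each visit. Assumed, because the document gives no values: visit correlation 0.70 to 0.85; 10 to 20% of controls seen at 4 months missing at 12; logistic drop-out slope on the 4-month score of 1 in controls and 0, 1 or 2 in the intervention arm; no mean change between visits. The two-visit likelihood estimate is b_arm + b_4 × (difference in 4-month means over all patients seen at 4 months), where b_arm and b_4 come from regressing the 12-month score on arm and 4-month score in completers. With this missingness pattern it is what a two-visit mixed model delivers.

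Bias in the 12-month difference, SD units:

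| Drop-out mechanism | Completers | Two-visit model |
|---|---|---|
| On 4-month score, same in both arms, no effect | about 0 | about 0 |
| On 4-month score, same in both arms, effect 0.30 | −0.015 to −0.027 | −0.002 to 0.002 |
| On 4-month score, intervention slope 0, no effect | −0.06 to −0.15 | about 0 |
| On 4-month score, intervention slope 2, no effect | +0.09 to +0.14 | about 0 |
| On the unseen 12-month score, intervention slope 0, no effect | −0.09 to −0.18 | −0.03 to −0.09 |

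Standard errors are about 0.12 to 0.14 for both methods, so the two-visit model costs essentially no precision. In the third and fourth rows carry-forward is off by 0.015 to 0.040 SD in absolute value.

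**5. Sensitivity to the loss rate.** 266 patients, correlation 0.8, true effect 0.30, slopes 1.2 in controls and 0.4 in the intervention arm:
- 12% loss in each arm: completers 0.24, random draw 0.24, two-visit model 0.30.
- 12% loss overall, rates free to differ by arm: completers 0.21, two-visit model 0.30.
- 3.75% loss (deaths between visits only): completers 0.264, two-visit model 0.298.
- 3.75% loss with equal slopes: completers 0.295, two-visit model 0.300.

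**The case against.** Several things can be said for the plan as written.

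- **The bias is conditional.** A reader might infer that drop-out depending on earlier cognition is enough to bias the comparison. It is not. With one mechanism in both arms the selection largely cancels, leaving 0 to 0.03 SD against a standard error of about 0.13. This stands.
- **Loss may be small.** On the document's rates only about 3 percentage points of mortality fall between the visits. Data collection has the assessor go to wherever the patient lives, and missing proxy data are collected by telephone. At 3.75% loss even the arm-differential scenario costs only 0.30 − 0.264 = 0.036 SD. This stands, but loss for reasons other than death is not stated.
- **The plan does use the 4-month score, and carry-forward can do tolerably.** With no average change between visits, as simulated, carry-forward was off by at most 0.04 SD. The objection to it rests on expected decline. The Discussion says of nursing-home residents and other markedly frail patients that they "are at high risk of developing dementia and of worsening of a pre-existing dementia"; it does not say that the whole trial population declines between 4 and 12 months. So the no-change assumption is unsupported in this population, not shown to be false.
- **Carry-forward and the dead.** A reader might infer that carry-forward gives scores to some 76 dead patients. It cannot; that figure belongs to the worst-score and random-draw imputations.
- **A mixed model is no cure for death.** It gains nothing from patients who die before 4 months, who are most of the deaths on these figures, and it implicitly extrapolates scores for those who die between visits. This stands and shapes the fix.
- **The results are secondary.** The Discussion treats significant secondary effects as hypothesis-generating if the main outcome is negative. This limits the importance of the point but does not remove it.

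**Conclusion.** The point holds in a conditional form. The plan commits to a completers-only main analysis at 12 months, although an earlier score on the same scale exists for patients seen at 4 months, and none of its three sensitivity analyses uses that score properly. Bias in the arm contrast is about 0.06 to 0.15 SD if drop-out among survivors depends on 4-month cognition differently by arm with 10 to 20% control loss, and it shrinks towards 0.04 SD or less if loss is close to the between-visit mortality. With a common mechanism it is negligible. These sizes rest on assumed correlation, loss and drop-out slopes; the document supplies none of them.

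A reader might infer that a two-visit model removes the problem altogether. It does so only under missing at random: 0.03 to 0.09 SD remained when missingness depended on the unseen 12-month score and differed by arm, and death needs its own rule. Still, the model needs a weaker assumption than the completers' analysis at no cost in precision, so it is the better main analysis for these secondary results. The primary 4-month conclusion is not affected.

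**What to change.** For the composite and other continuous outcomes measured at both visits:

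1. Make the main 12-month analysis a linear mixed model on the 4- and 12-month scores, with arm by visit, nursing-home stratum and unstructured covariance, including every patient with at least one visit. Report the 12-month contrast and state that it is valid under missing at random.
2. Keep the completers' analysis as a sensitivity analysis and drop carry-forward.
3. Do not impute scores for patients who have died. Restrict any worst-score or random-draw imputation to survivors with a missing assessment.
4. State the estimand for death, for example cognition among survivors with deaths by arm reported alongside. Say how patients who die between visits are handled, since otherwise the model extrapolates for them.
5. Note the limits: the model recovers nothing for deaths before 4 months and does not correct missingness that depends on the unseen 12-month score.

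Binary outcomes, and incident dementia (assessed at 12 months only), are outside this change and keep their own analyses.

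The cost is a few sentences and one standard model on data already scheduled for collection. Time plan of the study puts the 12-month analysis in spring 2013, after the 4-month analysis, so the change can be fixed before 12-month results are examined by arm.
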